### Procedures for missing, unused and spurious data

The standard method for dealing with loss to follow-up in smoking cessation trials is to assume that those lost-to-follow are continuing to smoke.[16] However, we will also use methods of multiple imputation as suggested by Hedeker[23] to explore the effect of assuming alternative associations between 'missingness' and smoking status as explained above.

### Definition of populations analysed

As this is an intention to treat analysis, all participants who cannot be contacted at follow up are assumed to be still smoking and all randomised participants are included in all analyses for trial outcomes. We will look for effect modification by actual redemption of NRT voucher and by the intensity of proactive counselling received.

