### Trial Groups

After randomisation, Essentia staff will be automatically guided through the correct intervention for each participant via four on-screen templates. The Essentia database will be configured so that only the template which corresponds to the appropriate treatment allocation can be used. Participants will be randomly allocated to either usual care (i.e. control group, called the 'Together Programme') which comprises reactive counselling or proactive counselling (intervention 1) as described below. Within these two groups there will also be random allocation of smokers to either being offered advice to obtain nicotine addiction treatment (i.e. NRT, Varenicline or Bupropion) from their general practitioner or local NHSSSs (control) or an offer of a voucher which can be redeemed at a pharmacy for a free supply of NRT (intervention 2). The aim is to have four trial groups of equal size.

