### Intervention 1 – Proactive telephone counselling

Smokers will be offered usual "Together Programme" written materials and modified email and text messages, plus a programme of proactive telephone counselling following an agreed protocol, delivered by specially-trained Essentia counsellors. After their initial counselling session, participants will receive another call for counselling prior to their quit date and also on the day that they stop smoking itself. Subsequently participants will be eligible to receive up to 4 further telephone counselling sessions in the 3 weeks after their quit date. Earlier sessions will help smokers to focus on and prepare for quitting and later ones will focus on remaining smoke-free and preventing relapse. This call pattern is based on a previously-trialled, US quitline calls schedule and the weekly contacts made after smokers' quit dates follow a similar frequency to that used for face-to-face counselling by many NHSSSs. During counselling and, if appropriate, smokers will be advised to obtain further support (including, potentially, nicotine addiction therapies) from their local NHSSSs or general practitioners. [name] (UCL – a protocol author) will develop the intervention protocol and train counsellors in proactive telephone counselling.

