### Intervention 2 – Provision of voucher for free NRT

During discussion of nicotine addiction treatments, callers will be offered a voucher which can be redeemed at a pharmacy for a cost free supply of NRT. Not all smokers will choose to accept the voucher. For example, some smokers might have previously used NRT, so that they do not believe using this again is likely to be effective. Others might prefer to try different treatments for nicotine addiction which can be obtained from other sources.

For smokers who choose to accept the offer of an NRT voucher, the Essentia counsellor will run through with them a checklist of cautions to NRT. This checklist will be identical to that which is in the product information that accompanies the over the counter (OTC) formulation of NRT used in the trial. If callers report uncertainties about any of the listed cautions applying to them, a voucher will not be issued and they will be advised to discuss the potential use of NRT with their GP. Vouchers will be generated electronically by the Essentia counsellor and sent to the pharmacy team responsible for voucher redemption and participants will be given a freephone number to call for voucher redemption. Confirmation of this number will sent by email, text or paper mail according to participants' preferences.

A 15 mg/16 hr transdermal nicotine patch which is available over the counter (OTC) and, hence, on the UK 'General Sales List' will be used and there are no specific recommendations regarding their purchase or storage. Although smokers in the UK can purchase such medication OTC, we propose that voucher redemption is overseen by a pharmacist to provide reassurance about trial safety. NRT will be stored securely within a Glasgow pharmacy and a secure system for recording i) when NRT has been issued against any one voucher and ii) the batch number of NRT sent to individuals will be used. The pharmacy team will be part of the NHS Greater Glasgow and Clyde's Public Heath Pharmacy Department.

Participants will be required to telephone the pharmacy team to redeem their voucher and obtain NRT and they will not be directly sent NRT without making such a request. Participants' vouchers will make them eligible for up to 6 weeks cost-free NRT treatment, supplied in batches. All NRT packaging and instructions will be identical to that which has been approved for retail sale on a General Sales License outside of pharmacies

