### Compliance

This is a pragmatic trial, testing the delivery of interventions in routine clinical use, using an intention to treat analysis. In such studies it is usual for participants to have variable compliance with interventions as their level of engagement with these is self selected. Consequently, uptake rates for interventions (e.g. the proportion of subjects who redeem NRT vouchers) are amongst study outcomes.

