### Potential problems with compliance

Participants randomised to receive proactive telephone support may not actually answer or be available for many of the calls that are made to them. If this situation were to arise, then it could attenuate any differences between interventions delivered to the control and intervention groups, making it harder to detect an effect attributable to the proactive call protocol. Additionally, participants who register for the Together Programme are currently able to telephone smoking cessation advisors whenever they wish and if a large number make such calls were to be made, this could further reduce differences between interventions. Consequently, treatment protocols in the reactive and proactive arms of the trial will need to be clearly defined.

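### Voucher redemption and counselling received arise after randomisation and only in the treated arms, so the planned effect-modification analysis cannot be estimated within its own factor and otherwise mixes treatment effect with self-selection

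*Protocol article*

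**What the plan says.** After confirming intention to treat, *Definition of populations analysed* adds: "We will look for effect modification by actual redemption of NRT voucher and by the intensity of proactive counselling received". *Statistical Analysis Methods* uses the same term for deprivation and there gives it its usual meaning: a test for interaction, asking whether each treatment's effect is similar in more and less deprived participants.

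The article describes the two uptake variables as follows.

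- **Redemption.** Only the two voucher-offer groups can hold a voucher (*Trial Groups*); the other two are advised to seek treatment elsewhere. Taking up the offer is voluntary: "Not all smokers will choose to accept the voucher". Acting on it takes a further step: "Participants will be required to telephone the pharmacy team to redeem their voucher and obtain NRT".
- **Counselling received.** The proactive programme belongs to the two proactive groups, and the number of sessions varies: "Subsequently participants will be eligible to receive up to 4 further telephone counselling sessions in the 3 weeks after their quit date". *Potential problems with compliance* warns: "Participants randomised to receive proactive telephone support may not actually answer or be available for many of the calls that are made to them".
- **Status of uptake.** *Compliance* says that "it is usual for participants to have variable compliance with interventions as their level of engagement with these is self selected", and that "uptake rates for interventions (e.g. the proportion of subjects who redeem NRT vouchers) are amongst study outcomes".

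The article names no method for the uptake analyses that would deal with self-selection.

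**The concern.** An effect modifier divides participants into subgroups within which the randomised groups can still be compared. It must therefore be defined in every compared arm and must not be a consequence of treatment. Deprivation meets both conditions. Redemption and proactive counselling received meet neither.

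What can be calculated in their place is a comparison of people who chose to engage with people who did not. Those who telephone a pharmacy or keep answering calls may be more motivated. Non-redeemers also include people refused a voucher because they were unsure about a caution, and people who preferred another treatment. For calls there is a second problem. Sessions continue for three weeks after the quit date, so someone who relapses early may stop answering, and abstinence then leads to calls rather than the reverse. The same could apply to later batches of NRT. It is much less likely for redemption recorded as yes or no.

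The trial is meant to inform which counselling the helpline offers and whether free NRT is worthwhile. A spurious gradient across uptake bears on exactly those questions.

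**Working it through.** The plan gives no figure for this analysis, so there is none to reproduce. The check has three parts.

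**1. Is the interaction estimable?** For the NRT factor, write offer *Z* (0/1) and redemption *R* (0/1). Only three cells can occur:

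| Cell | Intercept | Z | R | Z×R |
|---|---|---|---|---|
| No offer | 1 | 0 | 0 | 0 |
| Offer, not redeemed | 1 | 1 | 0 | 0 |
| Offer, redeemed | 1 | 1 | 1 | 1 |

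The last two columns are identical, so the matrix has rank 3 for 4 parameters and the interaction cannot be separated from *R*. The same holds for proactive allocation and intensity of proactive counselling, which is zero throughout the reactive arms.

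A cross-factor version asks whether the proactive effect differs by redemption within the offer arms. With terms for intercept, proactive allocation, offer, redemption and proactive × redemption, it has rank 5 for 5 parameters and can be computed. But proactive counselling may itself change who redeems, so proactive and reactive redeemers are not a randomised comparison.

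**2. What can the remaining contrast show when the offer does nothing?**

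Inputs from the document: comparison-group abstinence of 10% (*Sample Size and Justification*), and 2 × 644 = 1,288 participants with the offer and 1,288 without.

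Assumed, because the document gives no values: no true effect (10% with and without the offer), 50% redemption, and abstinence of 13% in redeemers and 7% in non-redeemers through motivation alone.

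- Consistency with no effect: 0.5 × 13% + 0.5 × 7% = 10%.
- Redeemers v non-redeemers: (0.13/0.87) / (0.07/0.93) = **1.99**.
- Redeemers v no offer: (0.13/0.87) / (0.10/0.90) = **1.34**.
- With 14% and 6% instead: (0.14/0.86) / (0.06/0.94) = **2.55**.

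To show a range, let a share *s* redeem and let redeemers' underlying odds of quitting be *k* times those of non-redeemers. The non-redeemer rate *q* and redeemer rate *r* then solve (1 − s)q + s·r = 0.10 with r/(1 − r) = k·q/(1 − q). The last column is the probability that redeemers and non-redeemers differ at two-sided p < 0.05, with 1,288·s and 1,288·(1 − s) participants.

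| s | k | Non-redeemers | Redeemers | OR, redeemers v no offer | OR, non-redeemers v no offer | P(p < 0.05) |
|---|---|---|---|---|---|---|
| 30% | 1.5 | 8.8% | 12.7% | 1.31 | 0.87 | 0.56 |
| 30% | 2 | 8.0% | 14.8% | 1.56 | 0.78 | 0.94 |
| 30% | 3 | 6.7% | 17.7% | 1.94 | 0.65 | 1.00 |
| 50% | 1.5 | 8.2% | 11.8% | 1.20 | 0.80 | 0.58 |
| 50% | 2 | 7.0% | 13.0% | 1.35 | 0.67 | 0.95 |
| 50% | 3 | 5.4% | 14.6% | 1.54 | 0.51 | 1.00 |
| 70% | 1.5 | 7.6% | 11.0% | 1.11 | 0.74 | 0.46 |
| 70% | 2 | 6.2% | 11.6% | 1.19 | 0.59 | 0.88 |
| 70% | 3 | 4.5% | 12.4% | 1.27 | 0.42 | 1.00 |

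At the self-report comparison rate in Table 1 of the article (14.5%), the same grid gives redeemer odds ratios from 1.12 to 1.97 and probabilities from 0.60 to nearly 1.00.

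No such calculation was made for counselling intensity. The design argument in part 1 covers it, but its size is not quantified.

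**3. What does an allocation-based estimate give in the same case?** The complier-average risk difference is the intention-to-treat difference divided by the redemption proportion: (10% − 10%) / 0.5 = 0, which is the truth under the assumptions. The price is precision. The standard error of the intention-to-treat difference is √(2 × 0.10 × 0.90 / 1,288) = 0.0118, a 95% half-width of 1.96 × 0.0118 = 2.3 percentage points. Dividing by 0.5 doubles this to about 4.6 points.

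**The case against.** The strongest reply is that this is one sentence about secondary analyses in a condensed article. The method could be left to an analysis plan that is not shown. The article is open that engagement is self-selected, lists uptake among process measures and outcomes, and keeps intention to treat as the primary analysis.

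Most of this is fair, and it limits the point. A reader might infer that the trial will report self-selection as a treatment effect. The document does not support that: nowhere does it say these results will be read causally or used to set call intensity or voucher policy. A within-arm contrast would also mix any real effect with selection, and need not be selection alone. Nor can one say that nothing in the sentence is estimable, because it does not state which effect is to be modified by which variable, and the cross-factor versions can be computed. The link from early relapse to fewer calls is plausible but is not stated in the document. The size shown above depends wholly on assumed values.

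The appeal to an unseen analysis plan does not stand. The article names both the analysis and the two modifiers, and no further detail can make the same-factor interaction estimable.

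There is also a fair objection to treating an instrumental-variable analysis as a complete remedy. Its exclusion restriction is doubtful here. Participants can obtain NRT elsewhere, and an offer might change that without any redemption. Proactive arms receive modified emails and texts and a different call protocol, so allocation acts through more than the number of calls. The fix allows for this.

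**Conclusion.** The sentence is wrong as written. Each treatment's interaction with its own uptake is not estimable; this follows from the design and needs no assumption. The contrasts that can be computed, including the cross-factor ones, condition on behaviour after randomisation and could show a benefit where none exists. With no true effect, 50% redemption and 13% v 7% abstinence, redeemers against non-redeemers gives an odds ratio of about 2.0, above the 1.5 the trial is designed to detect. Over 30% to 70% redemption and a prognostic odds ratio of 1.5 to 3, at 10% overall abstinence, that contrast reaches p < 0.05 with probability 0.46 to nearly 1.00. These sizes illustrate the risk and are not predictions.

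The primary intention-to-treat comparisons and the sample size do not use these variables and are unaffected.

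**What to change.** Delete the effect-modification sentence from *Definition of populations analysed* and put in its place:

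1. **Descriptive reporting.** Voucher redemption, calls received and abstinence by level of uptake within each arm, labelled as descriptive and not causal.
2. **Voucher, if an effect of receipt is wanted.** A complier-average effect of redemption, with randomised offer as the instrument. State the exclusion restriction (the offer affects abstinence only through redemption) and its weakness (NRT can be obtained elsewhere, so an offer may change other treatment use without redemption).
3. **Counselling, if an effect of receipt is wanted.** The same approach, with receipt of the proactive programme, defined before analysis, as the exposure. A raw call count is unsuitable because the content of calls and messages differs between arms. State the same caveat: allocation also changes emails and texts.

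The uptake data are already planned under *Process measures/measures of intervention uptake*. The cost is a change of wording and a little analysis work. The downside is a secondary estimate that is less precise (an interval about twice as wide at 50% redemption) and depends on assumptions that must be stated beside it.

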## Health Economic Analysis

The economic analysis will be presented separately for the within trial period (to summarise the observed evidence in relation to cost-effectiveness) and for a projected lifetime cost-effectiveness. Within trial analyses will be presented both to test the underlying hypotheses and to provide necessary parameter estimates for the lifetime cost-effectiveness model. Resource use and cost data collected and estimated within the trial will be used, together with the primary outcome measure (cessation), to produce an estimate of the incremental 'cost per quitter' (that is the additional cost of improving the quit rate). The incremental cost per quality adjusted life year (QALY) gained will also be estimated. It is likely that EQ5D will be insensitive to change, therefore, the EQ5D data will be more informative for the longer term modelling. Probabilistic sensitivity analysis will be undertaken to understand the uncertainty surrounding the cost effectiveness estimates[24].

A model, previously developed in a separate smoking cessation project [25,26], which describes the long term health benefits of quitting smoking in terms of QALYs saved and potential reduced costs to the health service, will then be analysed. Using this model, we will combine trial outcome data and previously determined cost data with estimates from the literature to extrapolate the cost effectiveness at six months to one year, and then to a lifetime. The lifetime analysis will produce estimates of cost per QALYs gained, thereby establishing the long term cost effectiveness of proactive versus reactive smoking cessation support, with or without the offer of NRT vouchers. Probabilistic sensitivity analysis will be used to characterise uncertainty in the parameters of the model driven by estimates obtained from the trial. Finally, measuring health status via EQ-5D will allow us to compare health-related quality of life for trial participants with population norms and allow us to undertake further sensitivity analysis within the long term model.

## List of abbreviations

RCT: andomised Controlled Trial; UK: United Kingdom; EQ5D: EuroQol 5 Dimensions; PIS: Patient Information Sheet; BMRB Social Research: British Market Research Bureau Social Research; UCL: University College London; GP: General Practitioner; CO: Carbon Monoxide
